#### tDCS.

The MBM-1 intelligent electrostimulator (Jiangxi Huaheng Jingxing Medical Technology Co., Ltd.) will be used, with 4.5 × 5.5 cm isotonic gelatin sponge electrodes soaked in saline (0.9% NaCl). Stimulation will target the dorsolateral prefrontal cortex (DLPFC) based on the EEG 10–20 system, with F3 as the anode and F4 as the cathode (**Fig 3**). Parameters: 1 mA current intensity (selected for safety and demonstrated behavioral effects) [25].Each session will last 20 minutes, with 5 sessions per week for 2 weeks.Ramp-Up/Ramp-Down: The current will gradually increase to 1 mA over the first 30 seconds and decrease to 0 mA during the final 30 seconds of each session. For sham stimulation, the device will activate for 30 seconds before automatically shutting down.

**Fig 3 pone.0342761.g003:**
[figure not shown]
Schematic diagram of the stimulation area for tDCS.

#### CCT.

The PASS-CATS 1.0 software will simulate cognitive tasks targeting learning/memory and executive inhibition.Learning/Memory Module: Object relocation, pattern recognition, novel character identification, numerical matching, mental arithmetic recall, and facial memory tasks.Executive Inhibition Module: Error detection, selective attention, symbol-number matching, linguistic inference, pattern reasoning, and numerical sequence tasks.Training sessions will last 30 minutes, administered 5 times per week for 2 weeks. The software will automatically record performance data, which will be scored by a blinded therapist.

### Outcome measures

#### Primary outcomes.

MoCA: will be administered at baseline, 4 weeks, and 12 weeks, with a focus on detecting mild cognitive improvements. The cutoff scores for cognitive impairment will be determined based on educational attainment (e.g., ≤ 13 points for primary education, ≤ 19 points for secondary education, and ≤24 points for tertiary education, as per the MoCA-Chinese version criteria).Prefrontal Cortex (PFC) Activation (fNIRS): Task-related oxygenated hemoglobin (HbO) signals will be measured using the NirSmartⅡ-3000D system (Huichuang Medical, Danyang), with wavelengths of 730 nm/850 nm and a sampling rate of 11 Hz. The channel configuration will consist of 22 channels using 8 emitters and 8 detectors (3 cm separation), aligned with the EEG 10–20 system (**Fig 4**).The protocol includes 8 minutes of resting-state data (eyes closed, seated comfortably in a quiet room). The Verbal Fluency Task (VFT) will involve 30 seconds of pre-task rest, 60 seconds of task phase (generate words starting with |d|, |g|, or |h|; 20 seconds per phoneme), and 75 seconds of post-task rest. The outcomes will include PFC activation intensity, resting-state functional connectivity (left/right PFC), and word-generation accuracy.

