Given the significant gap in research on combined tDCS-CCT intervention strategies, particularly the lack of systematic exploration into the differential effects between simultaneous and sequential intervention modes, this study will investigate the cognitive intervention effects of tDCS in stroke patients undergoing CCT. The primary objective will be to compare efficacy differences across various temporal combinations of tDCS-CCT therapies to identify the optimal synergistic protocol. Rooted in the theoretical framework linking tDCS-mediated cerebral hemodynamic modulation to cognitive enhancement, the study will specifically examine the association between prefrontal cortical oxygen metabolism and cognitive improvement. Functional Near-Infrared Spectroscopy (fNIRS) will be used to dynamically monitor pre- and post-treatment hemodynamic parameters in the prefrontal cortex, aiming to elucidate the neurophysiological mechanisms underlying cognitive recovery through the lens of neurovascular coupling.

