### Sample size estimation

Prior to study initiation, we will perform sample size estimation using G*Power 3.1.9.7 (Heinrich Heine-Universität Düsseldorf, Düsseldorf, Germany). The primary outcome will be the MoCA score, and the effect-size parameter will be set at Cohen’s f = 0.708, as reported in a peer-reviewed publication [17]. The statistical model will be a linear mixed model testing the group × time interaction. The following settings will be used: power = 0.95, α = 0.05, four groups, three repeated measurements (baseline, post-treatment, and follow-up), and a within-subject correlation of 0.30 (reflecting an expected increase in between-subject variability at follow-up). The software will indicate that a total of 48 participants will be required. Anticipating a 20% dropout rate, we will divide 48 by 0.8 and round up to the nearest multiple of four, resulting in a planned recruitment of 60 participants (15 per group).

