### Interventions

All participants will receive five sessions per week for two weeks, totaling 10 sessions. Adverse events will be monitored during each session, with researchers administering tDCS stimulation according to Brunoni et al.‘s protocol [23] to assess patient discomfort, pain, and any causality related to tDCS. Four treatment groups will be established:

Group A (tDCS-before-CCT): Patients will receive 20 minutes of tDCS, followed by 30 minutes of CCT after a 4-hour interval.Group B (tDCS-after-CCT): Patients will complete 30 minutes of CCT first, then will receive 20 minutes of tDCS after a 4-hour interval.Group C (tDCS-with-CCT): tDCS will be administered concurrently during the last 20 minutes of the 30-minute CCT session.Group D (CCT-only/Sham): Patients will undergo CCT with simultaneous placebo tDCS (sham stimulation).

Prior to the treatment intervention, patients will undergo a baseline assessment to determine eligibility. Enrollment will be based on the Montreal Cognitive Assessment (MoCA) [24]. Assessors will be blinded to group allocation. Post-treatment assessments will be conducted immediately after treatment completion, with follow-up assessments scheduled at 4 and 12 weeks post-treatment.The use of any non-invasive brain stimulation protocols other than those explicitly specified in this study (e.g., transcranial magnetic stimulation [TMS]) is strictly prohibited throughout the research period.

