#### Secondary outcomes.

Mini-Mental State Examination (MMSE): evaluates cognitive function (scored 0–30) and will be administered at baseline, 4 weeks, and 12 weeks. A score of ≥23 indicates normal cognition.Barthel Index (BI): evaluates activities of daily living (ADL) with dependency levels classified as follows: independent (100 points), mild dependency (61–99 points), moderate dependency (41–60 points), and severe dependency (≤40 points).Hamilton Anxiety Scale (HAMA):Scores ≥25 = severe anxiety; 21–24 = moderate anxiety; 14–20 = mild anxiety; 7–13 = borderline anxiety; < 7 = no anxiety.Hamilton Depression Scale (HAMD): Total scores: 0–54 (higher = worse). ≥ 25 = severe depression; 18–24 = moderate depression; 7–17 = mild depression.Follow-Up: MoCA and MMSE will be repeated at 4 and 12 weeks post-treatment to assess sustained cognitive improvements.

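### The primary outcome and its MoCA visits are stated inconsistently: MoCA alone in the sample size section, MoCA plus fNIRS/VFT measures in the outcome section, with a different set of visits

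*Protocol article*

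**What the plan says.** Four sections of the protocol article bear on the primary outcome.

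- **Sample size estimation** has one primary outcome: "The primary outcome will be the MoCA score". The model is a mixed model testing group × time, with "three repeated measurements (baseline, post-treatment, and follow-up), and a within-subject correlation of 0.30".
- **Interventions** describes the visits as: "Post-treatment assessments will be conducted immediately after treatment completion, with follow-up assessments scheduled at 4 and 12 weeks post-treatment". With baseline, that makes four. The sentence does not say which instruments are used at each visit.
- **Primary outcomes** (plural heading) has two entries. The first is MoCA: "MoCA: will be administered at baseline, 4 weeks, and 12 weeks". The second is prefrontal cortex activation by fNIRS, of which it says: "The outcomes will include PFC activation intensity, resting-state functional connectivity (left/right PFC), and word-generation accuracy".
- **Secondary outcomes** closes with: "MoCA and MMSE will be repeated at 4 and 12 weeks post-treatment to assess sustained cognitive improvements".

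The Introduction gives the only fNIRS timing in the text. The device is to "dynamically monitor pre- and post-treatment hemodynamic parameters in the prefrontal cortex".

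Under Statistical methods (Clinical data analysis), FDR adjustment is stated for between-group comparisons at individual timepoints. The same section refers to the primary outcome analysis in the singular, without naming the outcome or the visit.

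**The concern.** The trial is meant to identify the best timing of tDCS relative to CCT. That conclusion needs one agreed outcome, one agreed set of visits and one deciding comparison. As written, the sections can be followed in ways that give different trials.

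A team working from Primary outcomes would not collect the post-treatment MoCA, although the sizing model relies on it. A team working from Sample size estimation would collect it and would treat the fNIRS measures as non-primary. If the outcome section governs, two to four primary outcomes are tested at 0.05 with no stated order, co-primary rule or split of alpha. A positive finding on any one of them could then be reported as the primary result.

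**Working it through.** **1. Outcomes side by side**

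| Section | Primary outcome(s) |
|---|---|
| Sample size estimation | MoCA only |
| Primary outcomes | MoCA; PFC activation (fNIRS), with activation intensity, resting-state connectivity and word-generation accuracy |
| Statistical methods | Singular, not named |

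The outcome section can be read as two primary outcomes (its two entries) or as four (MoCA plus the three listed measures). Word-generation accuracy is a behavioural score from the verbal fluency task, not an optical signal, but it is listed under the fNIRS entry.

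**2. MoCA visits side by side**

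| Section | Baseline | Immediately post-treatment | 4 weeks | 12 weeks |
|---|---|---|---|---|
| Sample size estimation | yes | yes | one follow-up, week not given | (same single follow-up) |
| Interventions (instrument not named) | yes | yes | yes | yes |
| Primary outcomes | yes | no | yes | yes |
| Secondary outcomes (closing sentence) | – | – | yes | yes |

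Sample size estimation and Primary outcomes both count three measurements, but not the same three. The 4- and 12-week MoCA is primary in one section and appears under the secondary heading in the next. Primary outcomes also does not say from when its weeks are counted. Treatment lasts two weeks, so counting from baseline would place the visits two weeks earlier than the post-treatment count used elsewhere.

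The visit set changes the test. A group × time interaction has (k − 1)(m − 1) numerator degrees of freedom. With k = 4 groups this is 3 × 2 = 6 for three visits and 3 × 3 = 9 for four. With baseline, 4 and 12 weeks it is again 6, but the hypothesis no longer includes the immediate effect.

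There is a further consequence. If fNIRS is measured before and after treatment, as the Introduction says, and MoCA only at baseline, 4 and 12 weeks, the two entries under Primary outcomes share no visit after baseline.

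**3. Error rate across primary outcomes**

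The plan gives no figure for this, so there is none to reproduce. The input from the plan is the two-sided level of 0.05. For j independent outcomes with no true effect on any of them, the chance of at least one false positive is 1 − (1 − 0.05)^j:

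- j = 2: 1 − 0.95² = 0.0975, or 9.75%.
- j = 4: 1 − 0.95⁴ = 0.1855, or about 18.5%.

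The protocol gives no correlation between the outcomes, so a range is assumed. Simulation used 20,000 trials, four groups of 12 (the plan's 48 evaluable patients), one-way ANOVA on each of four outcomes and equal pairwise correlation:

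| Assumed correlation | At least one of four significant |
|---|---|
| 0.3 | 17.2% |
| 0.5 | 16.0% |
| 0.7 | 13.4% |

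At zero correlation the simulation returned 19.1% against the exact 18.5%, so these figures are good to roughly half a percentage point.

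**4. What an alpha split would cost**

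Take a single-visit one-way ANOVA with the plan's f = 0.708 and N = 48. The noncentrality is f²N = 0.708² × 48 = 24.06, with 3 and 44 degrees of freedom. Power is 98.5% at 0.05, 96.8% at 0.05/2 = 0.025 and 94.2% at 0.05/4 = 0.0125. The effect size is the one assumed for MoCA; the protocol gives none for the fNIRS measures.

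The sample size enters here only as 12 evaluable patients per group. Whether 48 follows from its stated inputs is a separate question and does not affect this point.

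**The case against.** The strongest reply is that the primary analysis is less open than it looks. Sample size estimation names MoCA and a group × time mixed model, and Statistical methods uses the singular. An omnibus interaction uses all visits, so it needs a fixed visit set more than a single primary visit. That stands. It narrows the defect to which visits enter the model, which contrast decides, and whether the fNIRS entry is primary.

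Second, Interventions does not name MoCA at the post-treatment visit, and the schedule in Fig 1 is not shown, so part of the visit grid cannot be checked. That also stands. The difference between Sample size estimation and Primary outcomes remains, because both concern MoCA.

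Third, the trial calls itself exploratory, and an alpha rule across outcomes may sit in an analysis plan that is not shown. This softens the multiplicity part. It does not reconcile sections of one document that disagree.

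Two stronger readings are tempting and not supported:

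- A reader might infer that every pairwise MoCA comparison at every visit is uncontrolled. Statistical methods attaches FDR to between-group comparisons at individual timepoints, so only the absence of a rule across outcomes is left.
- A reader might infer that the plan allows the primary result to be picked after the data are seen. Nothing states such an intent. Blinding keeps analysts masked until database lock, and the model for MoCA is named. Selective choice is a risk that the inconsistency leaves open, no more.

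**Conclusion.** The concern holds as a conflict within the document. The primary outcome list differs between Sample size estimation and Primary outcomes, and the MoCA visits differ across Sample size estimation, Interventions, Primary outcomes and Secondary outcomes. Followed literally, the outcome section drops a measurement that the sizing model uses.

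The size depends on how the outcome section is read. It is 9.75% for two primary outcomes and 18.5% for four, assuming independence, no true effects and each test at 0.05. For four outcomes it falls to about 13–17% at assumed correlations from 0.7 down to 0.3. The 18.5% is therefore the high end, not the expected value. All of these exceed the nominal 5%. The documents do not support saying that no primary analysis exists.

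**What to change.** 1. Keep MoCA as the single primary outcome, since it is the only one the trial is sized on, and list the fNIRS and verbal fluency measures as secondary mechanistic outcomes. If the investigators want them to stay primary, because the link between prefrontal oxygenation and cognition is a stated aim, state either a co-primary rule (all must succeed) or a split of alpha.
2. Write one identical MoCA visit set, including the immediate post-treatment visit and with weeks counted from the same point, in Sample size estimation, Interventions, Primary outcomes and Secondary outcomes. Check Fig 1 against it.
3. Name the one visit or group × time contrast that decides the primary result, and label the other MoCA visits accordingly. End of treatment is one defensible option: it appears in both Sample size estimation and Interventions, and it is not exposed to the remote self-administered assessment allowed at follow-up (Optimizing retention and follow-up adherence). A 4- or 12-week visit is also possible if durability is the main question.

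The cost is wording in the protocol and the registry entry. The article says that data collection had not begun at submission. If enrolment has since started, a dated amendment before database lock and unblinding would still serve, though a post-treatment MoCA not yet collected cannot be recovered. The fNIRS measures lose primary status or share alpha. With one primary outcome, alpha stays at 0.05 and this change requires no extra patients.

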**Fig 4 pone.0342761.g004:**
[figure not shown]
fNlRS Light Source Arrangement Diagram.

#### Secondary outcomes.

Mini-Mental State Examination (MMSE): evaluates cognitive function (scored 0–30) and will be administered at baseline, 4 weeks, and 12 weeks. A score of ≥23 indicates normal cognition.Barthel Index (BI): evaluates activities of daily living (ADL) with dependency levels classified as follows: independent (100 points), mild dependency (61–99 points), moderate dependency (41–60 points), and severe dependency (≤40 points).Hamilton Anxiety Scale (HAMA):Scores ≥25 = severe anxiety; 21–24 = moderate anxiety; 14–20 = mild anxiety; 7–13 = borderline anxiety; < 7 = no anxiety.Hamilton Depression Scale (HAMD): Total scores: 0–54 (higher = worse). ≥ 25 = severe depression; 18–24 = moderate depression; 7–17 = mild depression.Follow-Up: MoCA and MMSE will be repeated at 4 and 12 weeks post-treatment to assess sustained cognitive improvements.

### Safety and adverse event monitoring

Participant safety will be monitored continuously throughout the 1-week intervention period and the 2-month follow-up phase. All adverse events (AEs) and serious adverse events (SAEs) – whether reported by participants or observed by study investigators – will be systematically documented in accordance with established clinical research protocols.To monitor and manage adverse effects, patients will report sensations of itching, tingling, burning, headache, or other discomforts using a 4-point scale (1 = absent, 2 = mild, 3 = moderate, 4 = severe). The causal relationship between symptoms and tDCS stimulation will be assessed on a 5-point scale (1 = unrelated, 5 = strongly related).In the event of adverse events (AEs) or serious adverse events (SAEs), investigators shall provide immediate appropriate medical intervention and conduct follow-up assessments until clinical resolution or stabilization is confirmed. SAE data will be formally reported during regular meetings of the Data Safety Monitoring Board (DSMB) in compliance with institutional safety protocols.

### Optimizing retention and follow-up adherence

Participants will receive comprehensive information regarding trial procedures and expectations during the study period, with particular emphasis on the critical importance of follow-up compliance. A structured 3-month follow-up protocol will be provided to all patients,who will be strongly encouraged to attend scheduled clinic visits for face-to-face assessments. Two days prior to each follow-up appointment, designated research staff will proactively contact participants via telephone, WeChat, or alternative preferred communication channels to confirm attendance. For individuals unable to complete in-person evaluations, remote cognitive assessments will be facilitated through validated software platforms [https://doctor.shenzhenheling.com/],enabling flexible self-administration at the participant’s convenience. All remotely collected data will undergo immediate verification by research personnel, with subsequent outreach to be conducted as necessary to resolve missing or inconsistent responses. Participants retain the right to withdraw from follow-up procedures at any time without consequence to their standard medical care.

### Statistical methods

#### Clinical data analysis.

Statistical analyses will be conducted using SPSS 26.0, with a two-tailed significance level of p < 0.05. Categorical variables will be presented as frequencies and percentages, and compared using chi-square tests. Continuous variables will be assessed for normality using the Shapiro-Wilk test; normally distributed data will be reported as mean±SD, and non-normally distributed data as median [IQR].For repeated measures (e.g.,cognitive assessments at multiple timepoints), linear mixed models (LMM) will be used to include covariates (e.g., age, baseline scores, education level) and manage missing data. Between-group comparisons at individual timepoints will be conducted using one-way ANOVA for normally distributed data or Kruskal-Wallis tests for non-normal data, with multiple comparisons adjusted using the false discovery rate (FDR) method. Correlations will be analyzed using Pearson’s correlation for normally distributed data and Spearman’s correlation for non-normal data.The primary outcome analysis will be conducted on an intention-to-treat (ITT) basis [26]. Missing data will be addressed using complete case analysis if the missing rate is less than 5%, or multiple imputation if the missing rate is 5% or higher [27].

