### Participants

#### Inclusion criteria.

(a)Diagnosed with stroke (intracerebral hemorrhage or cerebral infarction) confirmed by head CT/MRI, per the 1995 Fourth National Cerebrovascular Disease Conference criteria;(b)Alert, hemodynamically stable, and capable of completing cognitive assessments;(c)First-time stroke within 3 months post-onset;(d)MoCA score between 10–26 (inclusive);(e)Voluntary informed consent.

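### A Shapiro-Wilk result chooses between ANOVA and Kruskal-Wallis for the per-visit arm comparisons, so one endpoint may be compared on different scales at different visits, without baseline adjustment

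*Protocol article*

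**What the plan says.** All of the rules are in the protocol article, mostly in Clinical data analysis.

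- Normality: "Continuous variables will be assessed for normality using the Shapiro-Wilk test". The result also decides whether mean with SD or median with IQR is reported. No other criterion is named. The text does not say whether the test is applied to all arms pooled, arm by arm, or to residuals.
- Test choice: "Between-group comparisons at individual timepoints will be conducted using one-way ANOVA for normally distributed data or Kruskal-Wallis tests for non-normal data". An FDR adjustment is attached to these tests, and the general level is stated as "with a two-tailed significance level of p < 0.05".
- Repeated measures: "linear mixed models (LMM) will be used to include covariates (e.g., age, baseline scores, education level) and manage missing data". No normality condition is attached to this model.
- Missing data: complete cases below 5% missing, "or multiple imputation if the missing rate is 5% or higher".

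Sample size estimation names MoCA as the primary outcome and the mixed-model group-by-time interaction as the test on which the trial is sized. It adds "Anticipating a 20% dropout rate". Clinical data analysis does not say which of the two analyses governs the MoCA conclusion.

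**The concern.** A two-stage rule lets a significance test on the outcome data select the next test and the effect measure. MoCA entry is restricted to scores of 10 to 26, and the article's Discussion expects ceiling effects, so the shape of the distribution may well change from visit to visit. One visit could then be reported as a difference in means and the next as a comparison of ranks, for the same endpoint and the same arms.

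The per-visit tests also discard information. One-way ANOVA and Kruskal-Wallis take no covariates, whereas the mixed model is to include baseline score, age and education. With 15 patients per arm, that precision matters. Because no analysis is named as decisive for MoCA, the unadjusted and switchable tests are not clearly subordinate to the model.

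**Working it through.** **The plan's own figure.** The documents give no figure for the pretest rule. The sample size belongs to the mixed-model test: with f = 0.708, noncentrality f²N = 0.708² × 48 = 24.06 on 6 and 88 degrees of freedom gives power 0.964, so N = 48 is reproduced, and 48 / 0.8 = 60. (This form of noncentrality does not use the stated correlation of 0.30. That is a separate matter and does not bear on this point.) The sizing therefore does not rest on the per-visit tests.

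**Inputs from the article.** Four arms of 15; two-sided 5% level; entry MoCA 10 to 26; 20% dropout, which leaves 48 of 60 at later visits. Sample size estimation and Primary outcomes each list three MoCA measurements, so two post-baseline visits are used. Interventions implies a third, immediately after treatment.

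**Assumed inputs.** MoCA SD 4 or 5; visit means 19/21/22 or 20/23/25; correlation 0.3 or 0.7; integer scores capped at 30; no arm effect. There were 1,500 simulated trials per scenario, with Shapiro-Wilk at 5%.

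**Different tests at the two post-baseline visits.** If the pretest rejects with probabilities p₁ and p₂, and the visits are treated as independent, the chance of different tests is p₁(1−p₂) + p₂(1−p₁).

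| Scenario (means; SD; correlation) | Pretest | p₁ | p₂ | Different tests |
|---|---|---|---|---|
| 19/21/22; 4; 0.3 | pooled | 0.070 | 0.079 | 0.14 |
| 19/21/22; 5; 0.3 | pooled | 0.075 | 0.163 | 0.21 |
| 20/23/25; 4; 0.7 | pooled | 0.107 | 0.492 | 0.49 |
| 20/23/25; 5; 0.7 | pooled | 0.143 | 0.710 | 0.65 |
| 19/21/22; 5; 0.7 | any arm | 0.190 | 0.188 | 0.31 |
| 20/23/25; 5; 0.3 | any arm | 0.248 | 0.535 | 0.52 |

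The rows include the lowest and highest value for each way of applying the pretest. A separate direct simulation at SD 4.5 gave about 18% to 53%.

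For exactly normal data the same formula gives 2 × 0.05 × 0.95 = 9.5% with a pooled pretest. With a per-arm pretest, the chance of any rejection at one visit is 1 − 0.95⁴ = 0.185, so the figure is 2 × 0.185 × 0.815 = 30%.

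**Error rates at the last visit, no arm effect.** ANOVA throughout: 0.041 to 0.055. Kruskal-Wallis throughout: 0.037 to 0.045. Two-stage rule: 0.041 to 0.055. The Monte Carlo standard error is about 0.006. ANOVA and Kruskal-Wallis disagreed on significance in 1.4% to 2.4% of these trials. The switch neither damages nor improves the type I error.

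**Precision.** Under assumed arm effects with SD 4.5, power at the last visit was 0.48 for the two-stage rule and 0.54 for a baseline-adjusted comparison at correlation 0.3; at correlation 0.7 it was 0.57 and 0.82. The direction follows from theory: adjustment multiplies the residual variance by about 1 − ρ², which is 0.91 at 0.3 and 0.51 at 0.7.

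**Imputation (conditional).** The anticipated 20% exceeds the 5% trigger. With 12 of 60 missing at the last visit, SD 4, 20 regression imputations and 400 trials per scenario, the imputed datasets disagreed on which test to use in 35% to 60% of trials (pooled pretest) or 66% to 81% (any arm). This assumes that the pretest is run in each imputed dataset.

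**The case against.** The strongest reply is that MoCA has a well-defined analysis whatever the pretest says. Sample size estimation names the mixed model for it, and Clinical data analysis assigns repeated cognitive assessments to that model, gives it the missing data to handle and applies no switch. This stands. A reader might infer that the MoCA endpoint has no defined result once imputation starts; the documents do not support that. Only the per-visit comparisons are exposed.

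Nor does the text say that normality is to be judged in each imputed dataset. It could be judged once on observed data, and such detail may sit in an analysis plan that is not shown. The 20% is a planning allowance, and the remote assessments offered under retention may keep missingness lower. The split across imputations is therefore a conditional consequence.

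Three other tempting readings also fail:

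- Inflated type I error: it stays near 5%.
- A contradiction in using a Gaussian mixed model beside rank tests: the model's assumptions concern residuals and random effects, so the two can coexist.
- Arm differences making the data look non-normal: this applies to a pooled pretest. A pure shift between arms cannot cause it when each arm is tested separately.

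Finally, the trial is labelled exploratory, and the rate of mixed tests is not a rate of wrong conclusions. Both are fair. They limit the severity but do not justify keeping a rule that brings no measurable gain and leaves the effect scale open.

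**Conclusion.** The point holds in limited form. The article fixes a data-driven choice of test and summary statistic for per-visit arm comparisons, these comparisons ignore baseline, and their standing relative to the mixed model is not stated. Different tests at the two post-baseline visits are likely enough to matter, at roughly 20% to 50% of trials and 14% to 65% across the scenarios tried, but they are not certain. These figures rest on assumed MoCA means, SD, shape and correlation, and on whether the pretest is pooled or per arm, which the text leaves open. The power comparison also rests on assumed arm effects, so its direction is firmer than its size.

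The harm is to consistent interpretation and precision, not to the validity of the tests. The change should be made, but the primary analysis does not fail without it.

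**What to change.** In Clinical data analysis:

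1. Delete the Shapiro-Wilk switch for outcome comparisons.
2. State that the planned linear mixed model decides MoCA.
3. Take baseline-adjusted between-arm contrasts, with confidence intervals, from that model at every visit. The planned FDR adjustment can be applied to these contrasts.
4. Check the model's residuals, for example graphically.
5. Name one robustness analysis, rank-based or permutation, and apply it in the same way at all visits whatever the residuals show.
6. Report mean and SD at every visit, with the median added where useful.

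With one method fixed in advance, neither visits nor imputed datasets can receive different tests. The cost is a wording change before database lock and minor analysis work, with no extra data or patients.

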### Study design

This is a single-center, double-blind, randomized controlled exploratory trial. Sixty patients will be randomly assigned to one of four groups (n = 15 per group). The protocol will be reported following Standard Protocol Items: Recommendations for Interventional Trials (SPIRIT) schedule statement(S1 File).Participant enrollment, randomization, assessment, and follow-up schedules are summarized in **Fig 1**.For a detailed visualization of the study workflow, **Fig 2**, which outlines the sequential steps from participant recruitment to final follow-up.

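### The mechanistic aim linking prefrontal oxygenation to cognitive gain rests on a plain correlation that ignores randomised arm; if arms are pooled, a shared treatment effect can imitate the link

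*Protocol article*

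**What the plan says.** The Introduction states that the trial will "specifically examine the association between prefrontal cortical oxygen metabolism and cognitive improvement". It gives the purpose as mechanistic: "aiming to elucidate the neurophysiological mechanisms underlying cognitive recovery through the lens of neurovascular coupling". The Primary outcomes section lists prefrontal activation by fNIRS beside MoCA, and the Discussion treats HbO as a marker that foretells cognitive recovery.

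The Clinical data analysis section has one sentence on association: "Correlations will be analyzed using Pearson" ("correlation for normally distributed data and Spearman" for the rest). It does not name the pair of variables, say whether change or level is meant, give a time point, or say whether the four arms are combined. Covariates are mentioned for a different analysis only, the repeated measures, where "linear mixed models (LMM) will be used to include covariates (e.g., age, baseline scores, education level) and manage missing data". The FNIRS data analysis section describes averaging HbO at group level and drawing maps; it gives no model that relates HbO to cognition.

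**The concern.** A correlation computed over all patients of a four-arm trial combines two things: how the arm means of the two measures line up, and how the two measures move together among patients within the same arm. The second bears more directly on the proposed mechanism. The first arises whenever treatment moves both measures in a similar pattern across arms, whether or not one has anything to do with the other.

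The sponsor's own theory, that tDCS alters cerebral haemodynamics and thereby cognition, leads one to expect arm effects on both measures. The more fully it holds at arm level, the less a pooled coefficient can tell a within-arm link from a shared treatment effect. What is at stake is the interpretation of the mechanistic result. The randomised comparison of timing strategies does not depend on it.

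**Working it through.** The protocol gives no figure for this analysis, so there is none to reproduce. The check asks how often a correlation would be significant with no within-arm association at all.

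**Inputs from the protocol.** Four arms of 15, N = 60 (Study design). Cohen's f = 0.708 for MoCA, and 48 patients required before a 20% dropout allowance (Sample size estimation). Two-sided 0.05 (Clinical data analysis).

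**Assumptions, not in the protocol.** The arms are pooled and the pair is MoCA change with HbO change. The MoCA figure, stated for a group × time interaction, is used as a between-arm f on one value per patient. The HbO effect size f_H and the correlation c between the two sets of arm means are unknown, so both are varied.

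**Expected pooled correlation.** With zero within-arm correlation,

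r = c · f_M · f_H / √[(1 + f_M²)(1 + f_H²)].

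With f_M = f_H = 0.708 and c = 1 this is f²/(1 + f²) = 0.501/1.501 = 0.334. At N = 60, t = 0.334 × √(58/(1 − 0.334²)) ≈ 2.70, p ≈ 0.009.

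**Rejection rates.** 20,000 simulated trials per setting, Pearson, N = 60, MoCA f = 0.708, within-arm correlation zero:

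| HbO f | Arm-pattern correlation c | Expected r | Pooled test significant |
|---|---|---|---|
| 0.708 | 1 | 0.33 | 78% |
| 0.708 | 0.5 | 0.17 | 24% |
| 0.708 | 0 | 0.00 | 4% |
| 0.40 | 1 | 0.21 | 39% |
| 0.25 | 1 | 0.14 | 19% |
| 0.25 | 0.5 | 0.07 | 8% |
| 0.10 | 1 | 0.06 | 7% |

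With 48 patients the top setting gives 68%. Spearman is inflated similarly there (73% to 78% at N = 60, 62% to 68% at N = 48, depending on the arm pattern).

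If both effects are smaller than planned, the problem shrinks quickly. With equal, aligned effects on both measures, rejection is 17% to 19% at f = 0.40 (N = 60, Pearson and Spearman), about 7% at f = 0.25 and about 5% at f = 0.10.

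**After adjustment for arm.** The partial correlation given arm has N − 5 = 55 degrees of freedom, against N − 2 = 58 for the plain one. Its rejection rate stays at about 5% in every setting, including f = 0.708 on both measures.

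**The by-arm reading.** Correlations within each arm are free of this problem. But with 15 patients a coefficient must exceed about 0.51 in absolute value to be significant at two-sided 0.05, and with 12 (15 less 20%) about 0.58, in four separate tests. The arm-adjusted test on all 60 needs about 0.26.

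**The case against.** The strongest reply is that the protocol never says the arms will be pooled, nor that the correlation sentence serves the aim in the Introduction. Correlations by arm would fit the same wording, and an article may leave the variable pair, time point and handling of arm to a fuller document. This stands as far as it goes: pooling and the HbO–MoCA pair are inferences from an unqualified sentence. It does not dispose of the point, because the protocol names its method, and neither a plain Pearson nor a plain Spearman coefficient can include arm. Pooled, the method mixes two kinds of association; by arm, it has little power.

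The second reply concerns size, and it also stands. The f of 0.708 is given for MoCA only. The 78% needs an equal HbO effect and perfectly aligned arm patterns, and the Discussion proposes different mechanisms for the three timings, with possible impairment when stimulation comes first. Alignment is therefore not a protocol assumption.

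Third, a reader might infer that the trial is set to report a false mechanism. The documents do not support that. If arms that gain more HbO also gain more MoCA, the pooled association is real; the mistake would be to read it as a within-arm link, and nowhere does the protocol say that a significant pooled coefficient will be taken as proof. The trial is also described as exploratory.

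**Conclusion.** The point holds in conditional form. A named mechanistic aim is paired with an association method that takes no account of randomised arm. If the arms are pooled, a treatment effect on both measures with a similar arm pattern can produce a correlation without any within-arm link.

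Under MoCA f = 0.708 and N = 60 the chance of this lies anywhere from the nominal 5% to 78%, and the protocol does not give the HbO effect or the arm pattern that would narrow the range. The 78% should be read as the top of the range examined, not as the expected rate. On either reading of the sentence, pooled or by arm, an arm-adjusted analysis serves the aim better. This is a cheap improvement to a secondary interpretation; it does not touch the validity of the primary comparison.

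**What to change.** State in advance one HbO variable, one cognitive variable and one time point for the association. Test it with a partial correlation given arm, or with a linear model of MoCA change on HbO change that includes arm as a factor, using one value per patient. Baseline MoCA and baseline HbO may be added for precision; the concern itself requires only arm. Report the unadjusted correlation as descriptive.

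The cost is three degrees of freedom for arm (five with both baselines, leaving 53 of 58 at N = 60) and slightly more analysis work in the software already named. No new data are needed, and the protocol says that data collection had not begun at submission.
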